**Ethics and dissemination:**

This study has received ethical approval from the NHS Research Ethics Committee: London-Camden and King's Cross (ref: 15/LO/0085). Study findings will be disseminated to healthcare professionals and scientists in the field through publication in peer-reviewed journals and conference presentations.

Strengths and limitations of this study
A strength of this study is that it will follow US Food and Drug Administration guidelines for the development of patient-reported outcome measures. Consequently, it will seek extensive input from service users, parents, families and those with experience of working with autism spectrum disorders.All participants will be asked to complete the study questionnaires twice allowing for an assessment of questionnaire sensitivity to change in this initial psychometric evaluation of the instrument.A potential limitation of this study is that study questionnaires will be completed in participants’ homes. One may be uncertain about the extent to which measures are completed independently. However, some participants will be completing questionnaires in clinic settings which will allow us to explore levels of support which informants require to complete the questionnaire.

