All participants will be asked to complete the questionnaire battery twice: at study entry and again between 4 and 6 months after initial completion. This is to allow for analysis of the stability of the questionnaire. Based on clinical experience, 4–6 months was chosen as an appropriate period of time in which one would anticipate change in symptoms (eg, in relation to treatment response). Information on treatment, diagnoses and other relevant information will be gleaned from medical records in order to estimate when change of scores would be expected.

Approximately 50 participants, along with their parent/carer/relative/partner, teacher/employer and clinician will be asked to complete the ACB and gold standard questionnaires (see table 1) again, 1 week after their initial completion, to provide a measure of test–retest reliability. However, interim analyses will be conducted after 25 participants have completed the measure at 1 week. If a statistically significant correlation is evident, no further participants will be asked to complete measures again after 1 week. Since some of the items measured in the ACB are likely to be related to changeable constructs, a priori decisions will be made about items in the ACB that are expected to remain stable over 1 week.

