###### Test–retest reliability

To assess test–retest reliability, intraclass correlation coefficients will be calculated on subscale and total scores which are expected to remain stable. As this is an exploratory study, weighted Cohen's κ values will be also calculated to assess test–retest reliability at the item level. Coefficients will be established separately for children and adults, and also for parent/carer/relative/partner, teacher/employer and clinician reports on samples of approximately 50 questionnaires completed approximately 1 week after initial completion. For scores that are expected to remain stable, we anticipate a high intraclass correlation of 0.80, for which a sample of 37 would provide a 95% CI of width 0.2. Intraclass correlation coefficients will also be calculated to assess the longer term stability of the measure 4–6 months after initial completion of the questionnaire.

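### The 4–6 month repeat is given conflicting purposes, and its only stated analysis, an ICC for stability, cannot show the sensitivity to change that the article lists as a strength

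*Protocol article*

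**What the plan says.** The Protocol article describes the same second completion in three ways.

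- **Strengths and limitations list (after the abstract).** Participants are "asked to complete the study questionnaires twice allowing for an assessment of questionnaire sensitivity to change in this initial psychometric evaluation of the instrument".
- **Phase 2, Main sample.** "All participants will be asked to complete the questionnaire battery twice: at study entry and again between 4 and 6 months after initial completion". The purpose follows: "This is to allow for analysis of the stability of the questionnaire". The next sentence gives the reason for the interval: "4–6 months was chosen as an appropriate period of time in which one would anticipate change in symptoms", with treatment response as the example. The section adds that records will supply treatment and diagnosis information, to judge when scores ought to change.
- **Test–retest reliability.** The analysis of these data is one sentence: "Intraclass correlation coefficients will also be calculated to assess the longer term stability of the measure", at the 4–6 month point. It names no subset of participants.

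Nothing else under Reliability, Validity or Factor analysis uses change scores, an external anchor of change, or a comparison of changed with unchanged participants.

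Two other sections bear on the point. The Aim says the scale should follow treatment response and be usable as a trial outcome. The closing Ethics and dissemination section leaves responsiveness after treatment to a later randomised trial.

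**The concern.** Stability of a measure is properly examined in people whose condition has not changed. Sensitivity to change is examined in people whose condition has changed, against some outside evidence of that change. The plan times the repeat for the second purpose, labels it with the first, and states only a statistic suited to the first.

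A 4–6 month ICC falls when error is large, and also when participants truly change by different amounts. A scale that follows real change can therefore look unstable, and a scale that misses real change can look stable. Neither result supports the listed strength. This matters because the scale is meant to track treatment response, and a reader would take the list as a promise that this study will provide first evidence of it.

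**Working it through.** **Plan's own figure.** The article gives no figure for the 4–6 month ICC. Its only ICC figure belongs to the 1-week retest: ICC 0.80, 37 participants, 95% CI of width 0.2. Bonett's formula is n = 8z²(1−ρ)²(1+(k−1)ρ)² / (k(k−1)w²) + 1. With z = 1.96, ρ = 0.80, k = 2 and w = 0.2 it gives 50.8, so 51. At n = 37 the exact F interval is 0.647–0.891, width 0.245. The figure does not reproduce for two occasions, but that is a separate matter and nothing below depends on it.

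**Step 1: what the ICC contains.** With equal variances and no mean shift, expected ICC = reliability × true-score correlation between occasions. Reliability 0.80 is the plan's anticipated 1-week value. The correlations are assumptions.

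- 0.80 × 0.9 = 0.72
- 0.80 × 0.7 = 0.56
- 0.80 × 0.5 = 0.40

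Taken alone, 0.56 also fits reliability 0.70 with correlation 0.80 (0.70 × 0.80 = 0.56), or reliability 0.56 with no true change.

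**Step 2: a mixed sample.** Assume true-score variance 1 and error variance 0.25, so reliability is 1/1.25 = 0.80. A proportion p improves by mean d with SD 0.5, independent of baseline. The variance of true change is V = 0.25p + p(1−p)d², and the mean shift is m = pd. The absolute-agreement ICC is 1/(1.25 + V/2 + m²/2).

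| p | d | V | m | ICC, all participants |
|---|---|---|---|---|
| 0.3 | 0.5 | 0.1275 | 0.15 | 1/1.3250 = 0.75 |
| 0.3 | 1.0 | 0.2850 | 0.30 | 1/1.4375 = 0.70 |
| 0.5 | 0.5 | 0.1875 | 0.25 | 1/1.3750 = 0.73 |
| 0.5 | 1.0 | 0.3750 | 0.50 | 1/1.5625 = 0.64 |

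In the unchanged participants the ICC stays at 0.80. The standardised response mean in the changed participants is d/√(0.25 + 2 × 0.25) = d/0.866, that is 0.58 for d = 0.5 and 1.15 for d = 1.0. The ICC does not report this.

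**Step 3: how far the 1-week ICC helps.** Dividing the 4–6 month ICC by the 1-week ICC estimates the true-score correlation: 0.56/0.80 = 0.70 for the scale that follows change, and 0.56/0.56 = 1.00 for the poor scale with no change. The two cases are separable in principle.

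With about 50 retests, the exact F 95% interval around 0.80 is 0.674–0.881. Treating 0.56 as known, the ratio runs from 0.56/0.881 = 0.64 to 0.56/0.674 = 0.83. It is less certain still if the retest stops after 25 participants, as the plan allows. The 1-week ICC also covers only scores expected to be stable. A ratio below 1 says that true scores moved differently between people, not that they moved with symptoms or treatment.

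**Step 4: precision in a smaller unchanged group.** At ICC 0.80 the exact F 95% interval has width 0.101 with 200 participants, 0.144 with 100 and 0.208 with 50.

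**The case against.** Several stronger readings are tempting, and the documents do not support them.

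- **That the plan specifies an ICC over all participants and discards the record information.** The Main sample section has everyone repeat the battery, and the reliability section names no subset, so an overall ICC is the natural inference. It is not a stated choice. The article collects record information to judge when change is expected and does not say how it will be used.
- **That the repeat answers no question.** The ICC does describe how stable scores are over 4–6 months.
- **That the plan penalises a responsive scale.** No threshold, pass/fail rule or item decision is tied to this ICC. The anticipated 0.80 is given for scores expected to be stable at the 1-week retest.
- **That error and true change are wholly confounded.** The 1-week ICC separates them in part, as shown in step 3.

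It can also be argued that a condensed article leaves the choice of change statistic to a fuller plan, and that responsiveness is deferred to a later trial. The first argument would dispose of a complaint about missing detail alone. It does not dispose of a stated interval, purpose and statistic that do not fit one another. The second has weight, but the deferral concerns change after intervention in a randomised trial. The strengths list still claims an assessment in this study.

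The practical objection stands. Clinicians are named for the 1-week repeat but not explicitly for the 4–6 month one, so the CGI may not be repeated. Clinic recruitment, intended to secure access to notes, is targeted at about 75%, or 150 of 200. The treatment report form is not validated.

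**Conclusion.** The point holds in a limited form. The article gives the 4–6 month repeat conflicting purposes, and the one stated analysis does not deliver the sensitivity to change claimed as a strength. A low ICC would mix true change with instability of the measure, only partly separable with the 1-week data, and no value of the ICC would show responsiveness.

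Under the assumptions in step 2, the overall ICC would be 0.64–0.75 for a scale whose ICC in unchanged participants is 0.80. The proportions and sizes of change are illustrative and not taken from the article. The direction follows from the structure of the ICC once participants change by different amounts. This should be corrected, but it does not undermine the rest of the validation.

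**What to change.** State one purpose, or two separate ones, for the 4–6 month repeat, and match the analysis to it.

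1. Before analysis, define unchanged and changed participants, using medical records, the treatment report form, the comparator scales and, if completed at both times, the CGI.
2. Report the 4–6 month ICC in unchanged participants, beside the overall ICC and the 1-week ICC.
3. Assess sensitivity to change by correlating ACB change with change in the Achenbach and Aberrant Behaviour Checklist scores, and by comparing ACB change in changed and unchanged participants. Where a comparator scale has been used to define the groups, do not present its correlation with ACB change as independent confirmation.
4. If this is not intended, remove the sensitivity-to-change claim from the strengths list, in line with the deferral in the closing section.

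The cost is mainly wording and some added analysis of a battery already due to be repeated. The unchanged subgroup will be smaller. If half of the roughly 100 adults or 100 children are unchanged, the 95% interval at ICC 0.80 widens from 0.144 to 0.208. Anchors will be incomplete for participants without accessible records or a repeated CGI, so the number classified should be reported.

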###### Inter-rater reliability

Intraclass correlations will be used to assess inter-rater agreement between pairs of scores provided by two different raters (eg, self-report vs parent/carer; parent/carer vs teacher). Coefficients will be calculated at the subscale and total score levels. As this is an exploratory study, weighted Cohen's κ values will also be calculated to assess inter-rater reliability at the item level.

##### Validity

Scale comparisons will be used to investigate the concurrent convergent validity of the ACB. Pearson correlation coefficients will be calculated to explore the association between ACB scores and other measures collected that are commonly used in clinical practice (table 1; subscale scores will be investigated where appropriate).

Receiver operating characteristic (ROC) analyses will be conducted to evaluate the discriminative power of the instrument. Currently, there is no existing gold-standard instrument for the identification of concerning behaviour in ASD. Therefore, ROC analyses will be conducted using scores from the Achenbach suite of measures (Child Behaviour Checklist;^28^ Youth Self-Report;^28^ Adult Behaviour Checklist;^29^ Adult Self-Report^29^), and the Aberrant Behaviour Checklist^30^ collected as part of the validation phase of this study (see table 1). Where data are available, ROC analyses will also be conducted according to the presence or absence of clinical and/or the structured DAWBA diagnosis taken from the patient's medical notes. For clinical cut-offs, we are able to estimate the ROC against the structured psychiatric assessment with a 95% CIs of ±0.12 (assuming a false-positive rate of 20% and true-positive rate of 28%^31^). In addition, independent samples t tests will be performed with grouping variable DAWBA and/or clinical diagnoses (coded 1 for positive and 0 for negative diagnosis) to assess differences in ACB scoring and the ability of the ACB to distinguish between different groups of patients.

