ACB, Assessment of Concerning Behaviour Scale; ASD, Autism Spectrum Disorders; ICC, Intraclass Correlation Coefficient.

Participants’ questionnaire battery will be presented in HealthTracker™, a web-based platform for online completion (www.healthtracker.co.uk) that is currently being used in two EU FP7 projects—the Suicidality: Treatment Occurring in Paediatrics (STOP study; http://www.stop-study.com) and the Managing the Link and Strengthening Transition from Child to Adult Mental Health Care (MILESTONE) project (http://www.milestone-transitionstudy.eu). HealthTracker™ has also been used in a previous questionnaire development and validation study.^25^ The web-based questionnaires will follow the principles of data protection, security levels for health data, have an audit trail and Good Clinical Practice compliance. Participants will be given a unique ID number and log-in information, and will be asked to complete the questionnaires independently. All participants, including those with literacy issues, will have the option of going through the questionnaires over the phone with a member of the research team. Participants will also be able to complete paper versions of the questionnaires if requested. Questionnaire completion should not take longer than approximately 60 min for adults and 40 min for children.

Participant medical records will be accessed to validate the ACB against details of diagnoses obtained from patient case notes as well as against Development and Well-being Assessment (DAWBA^26^) diagnoses, IQ and treatment/medication status if they are available in case notes. Consent will be obtained to access medical notes. For children recruited via schools, the research team will also request details about IQ, educational attainment and diagnoses from school records. Parental consent will be obtained to do this. Where measures of IQ are not available from participant medical/school records, a brief measure of IQ will be collected by the research team (see table 1).

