##### Phase 2 recruitment

###### Main sample

Individuals with ASD (children, young people and adults) and their parents/caregivers/relatives/partners, teachers/employers and clinicians will be invited to take part (see below for inclusion criteria). Individuals with ASD will be recruited via clinician/researcher invite as well as via poster advertisements within healthcare and community settings, social media and websites for ASD support groups. Individuals with ASD will also be recruited from autism-specific schools and residential settings. Researchers will primarily be recruiting participants via clinics within participating trusts; the aim is to recruit approximately 75% via this method. This is to ensure access to medical notes for as many participants as possible. However, participants will not be excluded if they are not currently under the care of participating trusts. Parental consent will be obtained to request details about the child's IQ, educational attainment and diagnosis from school records.

Parents of children with ASD will be asked to provide details of their child's teacher and clinician, and will provide consent for the research team to contact them and invite them to complete the study questionnaires. Adults with ASD will be asked to provide details of another person who knows them well (either a parent/caregiver/relative/partner) who would be able to complete a questionnaire about them. Adults with ASD will also be asked to provide contact details for their clinician and their employer (if applicable and appropriate).

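### The secondary ROC against clinical/DAWBA diagnosis uses only participants with a diagnosis already on file; if availability rises with ACB score, cut-off sensitivity is overstated and specificity understated, and no correction is planned

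*Protocol article*

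**What the plan says.** The Validity section plans ROC analyses against two kinds of reference. The first is the Achenbach suite and the Aberrant Behaviour Checklist, which the study collects. The second is diagnosis: "Where data are available, ROC analyses will also be conducted according to the presence or absence of clinical and/or the structured DAWBA diagnosis", taken from medical notes.

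The Main sample section of Phase 2 says that the ACB will be validated against case-note diagnoses and against "Development and Well-being Assessment (DAWBA^26^) diagnoses, IQ and treatment/medication status if they are available in case notes". The DAWBA is not among the instruments in Table 1. For children recruited through schools, diagnoses are also requested from school records.

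On recruitment through clinics in participating trusts, the article says "the aim is to recruit approximately 75% via this method. This is to ensure access to medical notes for as many participants as possible". Others may join "via poster advertisements within healthcare and community settings, social media and websites for ASD support groups", or through autism-specific schools and residential settings, and "participants will not be excluded if they are not currently under the care of participating trusts".

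The one ROC precision statement concerns the diagnosis-based analysis at clinical cut-offs: "we are able to estimate the ROC against the structured psychiatric assessment with a 95% CIs of ±0.12", at an assumed false-positive rate of 20% and true-positive rate of 28%. The t tests in the same section code diagnosis as 1 or 0, with no code for a person who was never assessed.

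**The concern.** The ACB is meant as a screening measure, so sensitivity and specificity at a cut-off matter to its users. For the diagnosis-based ROC, the study neither assesses everyone nor assesses a random subset. It uses whatever routine care has left on file and drops the rest.

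Someone whose behaviour caused concern is more likely to have been assessed, and is also likely to score higher on a scale of concerning behaviour. If that holds within diagnosis groups, the analysed set contains too many ACB-positives in both groups. More of the diagnosed then appear to be detected, and more of the undiagnosed appear to be false positives. This is partial-verification bias. A confidence interval for sampling error does not cover it, and the area under the curve would hardly show it.

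**Working it through.** **Inputs from the article.** Main sample 200; clinic recruitment target about 75% (about 150 of 200); true-positive rate (TPR) 28%; false-positive rate (FPR) 20%; stated half-width 0.12.

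**Inputs assumed.** r, the chance of a result on file in ACB-positives divided by that in ACB-negatives, the same in both diagnosis groups; and prevalence of a co-occurring diagnosis, taken as 40% where needed. The article gives neither.

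**1. The plan's own figure.** The half-width of ±0.12 cannot be reproduced outright, because the number with a reference diagnosis is not stated. Solving n = 1.96² × p(1 − p) / 0.12² gives:
- p = 0.28: n = 3.8415 × 0.2016 / 0.0144 ≈ 54 diagnosed participants;
- p = 0.20: n = 3.8415 × 0.16 / 0.0144 ≈ 43 undiagnosed participants.

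The figure is therefore compatible with a sampling error for a proportion. It makes no allowance for who is missing.

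**2. Apparent rates among those verified.** Apparent TPR = TPR·r / (TPR·r + 1 − TPR), and likewise for FPR.

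| r | Apparent TPR | Apparent FPR |
|---|---|---|
| 0.67 | 0.188/0.908 = 0.207 | 0.134/0.934 = 0.143 |
| 1.0 | 0.280 | 0.200 |
| 1.2 | 0.336/1.056 = 0.318 | 0.24/1.04 = 0.231 |
| 1.5 | 0.42/1.14 = 0.368 | 0.30/1.10 = 0.273 |

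For r of 1.2 to 1.5 the shifts are 0.04 to 0.09 in TPR and 0.03 to 0.07 in FPR. For a better-performing scale (sensitivity and specificity both assumed to be 0.80), r = 1.25 gives 0.833 and 0.762, and r = 1.5 gives 0.857 and 0.727.

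**3. How large r can be.** At 40% prevalence, the ACB-positive share is 0.4 × 0.28 + 0.6 × 0.20 = 0.232. If every ACB-positive is verified and 75% are verified overall, the ACB-negative rate is (0.75 − 0.232)/0.768 = 0.674, so r cannot exceed 1/0.674 ≈ 1.48. An r of 1.5 needs at most 0.232 + 0.768/1.5 = 74% verified. An r of 2 needs at most 0.232 + 0.768/2 = 62%.

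**4. Whether a correction recovers the truth.** Take 200 people at 40% prevalence, with verification rates of 0.90 in ACB-positives and 0.60 in ACB-negatives (r = 1.5).
- Full counts: diagnosed 22.4 positive and 57.6 negative; undiagnosed 24 positive and 96 negative.
- Verified counts: 20.16, 34.56, 21.6 and 57.6, or 133.92 in all (67%).
- Available-case TPR: 20.16/54.72 = 0.368.
- Begg–Greenes applies the verified diagnosis rates to all ACB-positives and all ACB-negatives: 46.4 × 20.16/41.76 = 22.4 and 153.6 × 34.56/92.16 = 57.6. The corrected TPR is 22.4/80 = 0.28.

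**5. Simulation.** With 200 participants, 2,000 repetitions, 40% diagnosed and r about 1.5, available-case sensitivity was 0.36 against a true 0.28, and specificity 0.73 against 0.80. Inverse-probability weighting on the ACB and one comparator score returned 0.28 and 0.80. The area under the curve changed by 0.007 or less. In a separate simulation with 75% verified and sensitivity and specificity of 0.80, it fell from 0.883 to 0.857 at worst. When severity was unrelated to the ACB within diagnosis groups, there was no bias.

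**The case against.** A reader might infer more than the article supports.

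- **That the direction is known.** It is not. The link between severity and availability is an inference. If availability depended on diagnosis alone, sensitivity and specificity would be unbiased. If the highest scorers were the ones without notes, the direction would reverse. The Introduction's remark on population and clinic-based samples concerns prevalence, which by itself does not bias either measure.
- **That the error exceeds the stated ±0.12.** The FPR shift reaches 0.13 only at r = 2, which needs about 62% or fewer verified. The article states no such share. With 75% verified, the ceiling on r is about 1.48, and the shifts there are about 0.085 and 0.07.
- **That only people with a DAWBA count.** Clinical diagnoses from notes also count, and diagnoses are requested from school records for children recruited through schools. Both raise the verified share.
- **That the discrimination analysis as a whole fails.** The ROCs against measures collected in the study are untouched, the diagnosis-based ROC is additional, and the area under the curve barely moves.

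Two further objections have force. If a person with no recorded diagnosis were coded 0, the problem would be misclassification of the reference, which weighting does not repair. Weights that use recruitment source also fail if a route has no verified participants. The simulation's clean recovery reflects verification that was generated from the same scores used for weighting.

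Handling of missing reference results could be left to an analysis plan. Here, however, the article itself fixes the available-case rule, so the point can fairly be raised.

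**Conclusion.** The concern holds in conditional form. The article restricts the diagnosis-based ROC to people with a reference diagnosis on file, leaves that availability to routine care and recruitment route, and describes no correction. If r exceeds 1, sensitivity at a cut-off is overstated and specificity understated. For r of 1.2 to 1.5 at the plan's rates, TPR appears as 32–37% instead of 28%, and FPR as 23–27% instead of 20%. These sizes rest on an assumed r that is equal in both diagnosis groups. The upper end also needs slightly under 75% verified at 40% prevalence. The point is confined to cut-off performance in a secondary analysis, but this is the only ROC for which the article states a precision.

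**What to change.** In the Validity section:

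1. Keep the available-case ROC, but label it as applying to participants with a diagnosis assessment on file. Report how many lacked one, by recruitment route and by child or adult.
2. Treat people who were not assessed as missing, not as 0.
3. Add a verification-bias-corrected estimate of sensitivity and specificity beside it. This can be Begg–Greenes, or inverse-probability weights from a small model with ACB score, one comparator score and child/adult, with bootstrap confidence intervals. Include recruitment source only where each route has verified participants.

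The cost is analysis wording and modest programming, since the scores are already collected on the main sample. The correction assumes that availability depends only on the measured scores. If it also depends on diagnosis at a given score, the corrected figure carries an error of its own, so both estimates should be shown. Intervals may be wider.

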### Aim

This protocol outlines the intended development and validation of the ‘Assessment of Concerning Behaviour Scale’ (ACB). The term ‘concerning behaviour‘ was chosen for the title of the questionnaire based on feedback from patient and public involvement panels (PPI panels; including parents of individuals with ASD and individuals with ASD) who disliked the use of the other terms including ‘psychopathology’, ‘abnormal behaviour’, ‘maladaptive behaviour’, ‘symptoms’, ‘challenging behaviour’ and ‘mental health problems’.

The ACB aims to be a multidimensional screening measure of concerning behaviours in ASD. The measure is not intended as a diagnostic tool of co-occurring conditions, but aims to identify the presence of symptoms that may require further, more in-depth assessment. The measure will assess the severity of concerning behaviours to allow for assessment of symptom severity and treatment response over time. It is intended primarily for clinical use, but will also be appropriate for use as an outcome in clinical trials.

The study aims to develop self-report, parent/carer, teacher/employer and clinician report versions that can be used across the lifespan and spectrum of intellectual ability. The aim is to make the resulting questionnaire approximately 40 questions in length that should not take longer than 20 min to complete.

This project is being conducted as part of a larger National Institute for Health Research (NIHR)-funded research project entitled ‘Improving Autism Mental Health’, reference number: RP-PG-1211-20016.

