##### Phase 2 sample size

###### Main sample

For this stage of the study, we will aim to recruit 200 people with ASD (approximately 100 adults and 100 children), in addition to their parent/carer/partner, teacher/employer and clinician, to complete the ACB and gold standard measures for analysis of reliability and validity of the ACB (see table 1). In a population cohort of people with ASD, the approximate IQ distribution was as follows: 15% had IQ<50, 40% had 50<IQ<70, 40% had an average IQ (70<IQ<115) and 5% had an above average IQ (IQ>115).^18^ We will aim to recruit across the spectrum of IQ in similar proportions to this population sample to provide a representation of a ‘typical’ ASD population, and ensure generalisability of findings. Attempts will be made to obtain estimates of IQ for individuals with ASD from school/medical notes. However, where this is not available, the research team will collect a brief measure of IQ through completing the Wechsler Abbreviated Scale of Intelligence^27^ during brief home visits to participant homes. All parents, caregivers, relatives and partners will be asked to provide an estimate of the cognitive functional age of the individual with ASD on their demographic questionnaire.

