## Ethics and dissemination

This study has received ethical approval from the NHS Research Ethics Committee: London-Camden and King's Cross (ref: 15/LO/0085) and is currently recruiting participants. The aim of the study is to develop and validate an instrument to assess mental health and concerning behaviour in ASD. The study output will provide a clinically relevant tool, predominantly for use with individuals with ASD. Future research will require the recruitment of a second sample of participants in order for Confirmatory Factor Analysis to be conducted on the proposed factor structure resulting from this study. It is also hoped the instrument will be effective as an outcome measure for use in ASD intervention research. If the instrument is found to be a valid measure of concerning behaviour in ASD, future research will also need to assess the sensitivity of the instrument to change following intervention in a randomised controlled trial. The findings of this study will be disseminated to healthcare professionals and scientists in the field through publication in peer-reviewed journals and conference presentations.

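### An ACB cut-off derived from the ROC would be judged in the participants who produced it, and the stated ±0.12 does not cover the resulting optimism

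*Protocol article*

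**What the plan says.** Under Aim, the ACB is a screening measure, not a diagnostic one, that "aims to identify the presence of symptoms that may require further, more in-depth assessment". Under Validity, ROC analyses are planned against the Achenbach measures and the Aberrant Behaviour Checklist. In addition: "Where data are available, ROC analyses will also be conducted according to the presence or absence of clinical and/or the structured DAWBA diagnosis". On precision the section says: "For clinical cut-offs, we are able to estimate the ROC against the structured psychiatric assessment". The half-width given is ±0.12, and the rates behind it are stated as "assuming a false-positive rate of 20% and true-positive rate of 28" (per cent). The number of participants behind that interval is not stated, and neither is a rule for choosing a cut-off.

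The data available for this are:

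- **Main sample:** "200 people with ASD (approximately 100 adults and 100 children"), who complete the ACB and the reference measures in Table 1. On recruitment through clinics, which secures access to medical notes, "the aim is to recruit approximately 75% via this method".
- **Augmented sample:** 150 further children and 150 further adults, who complete the ACB only.
- **A later sample:** under Ethics and dissemination, "Future research will require the recruitment of a second sample of participants in order for Confirmatory Factor Analysis to be conducted". Cut-offs are not mentioned there.

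**The concern.** A new instrument has no established threshold. If one is read off the ROC curve, the chosen point tends to be one where chance variation in the sample happened to be favourable. Its sensitivity and specificity in that sample are then higher, on average, than in new patients. The augmented sample cannot correct this because it has no reference measure, and the later sample is named only for the factor structure. The ±0.12 expresses sampling error around a cut-off known in advance. It does not include the effect of having chosen the cut-off.

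At stake is the accuracy attached to a screening threshold. If sensitivity is overstated, users will miss more people who need fuller assessment than the published figure suggests. The authors already accept that a data-derived factor structure needs new participants. The same reasoning applies to a data-derived cut-off.

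**Working it through.** **1. Inputs.** From the article: main sample 200, about 100 per age group; about 75% via clinics, so 0.75 × 200 = 150; half-width 0.12; stated rates 20% and 28%. Assumed, because the article does not give them: 100 to 200 participants in the ROC analysis, 28% positive, equal-variance normal scores, and the cut-off rule.

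**2. The article's ±0.12.** The half-width for a proportion is 1.96 × √(p(1−p)/n). Because n is not given, the figure cannot be reproduced uniquely. Several readings come close:

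- p = 0.80 (or 0.20) in 42 positives (28% of 150): 1.96 × √(0.16/42) = 0.121.
- p = 0.28 in 56 positives (28% of 200): 1.96 × √(0.2016/56) = 0.118.
- The difference 0.28 − 0.20 with 100 per group: 0.118.

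All of them treat the cut-off as fixed.

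**3. Optimism under a Youden rule.** For each of 3,000 simulated samples per setting, the cut-off maximising sensitivity plus specificity was chosen in the sample. Optimism is the apparent value minus the true value at that cut-off. Results for AUC 0.80 and 28% positive:

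| N | Positives / negatives | Sensitivity overstated | Specificity overstated | Half-width, sensitivity (p = 0.80) | Ratio, sensitivity |
|---|---|---|---|---|---|
| 100 | 28 / 72 | 0.073 | 0.021 | 0.148 | 0.49 |
| 150 | 42 / 108 | 0.057 | 0.017 | 0.121 | 0.47 |
| 200 | 56 / 144 | 0.048 | 0.015 | 0.105 | 0.46 |

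At a standardised difference of 1.2 (AUC about 0.80) the best true sensitivity is 0.726. Using that in place of 0.80, the half-widths for 28, 42 and 56 positives are 0.165, 0.135 and 0.117, and the ratios are 0.44, 0.42 and 0.41. Hence roughly 0.4–0.5.

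For specificity at p = 0.80, the half-width with 144 negatives is 1.96 × √(0.16/144) = 0.065, and 0.015/0.065 = 0.23.

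**4. Like for like on the sum.** With 200 participants and 40% positive, sensitivity plus specificity is overstated by 0.058. The half-width of that sum is 1.96 × √(0.726 × 0.274 × (1/80 + 1/120)) = 0.126, and 0.058/0.126 = 0.46. The sum should be compared with this 0.126, not with a half-width for a single rate.

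**5. Sensitivity to the assumptions.**

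- Another rule: taking the first cut-off that reaches 80% sensitivity (AUC 0.80, 28% positive), sensitivity is overstated by 0.029, 0.019 and 0.013 at N = 100, 150 and 200, and specificity by essentially nothing.
- Discrimination: at N = 150 and 28% positive, the Youden rule overstates sensitivity by 0.079 at AUC 0.54 and 0.048 at AUC 0.90.
- Few positives and weak discrimination: with 20% positive and AUC 0.54, the overstatement is 0.120 at N = 100 and 0.139 at N = 75. The half-widths there are 0.175 and 0.202, so ±0.12 would not apply in any case.
- Coarse scores: with score steps of 1/8 standard deviation, a standardised difference of 1.2, 100 participants and 30% positive, the summed overstatement falls from 0.092 to 0.075.

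**The case against.** The strongest reply is that Validity states its purpose as evaluating discriminative power and speaks of estimating the ROC. It does not say that a data-chosen threshold will be published with uncorrected accuracy. The AUC of a fixed score does not depend on any cut-off. A journal article may also leave the selection rule and any resampling to a fuller document. The study describes its psychometric results as initial and some analyses as exploratory, and a positive screen leads only to further assessment.

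Much of this stands, and it limits the point in two ways.

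- A reader might infer that cut-offs must be chosen and judged in the same people. The article does not say so: a pre-fixed cut-off or an internal correction remains possible.
- A reader might also infer that the optimism is as large as the stated ±0.12. That does not follow. It arises from setting a sum of two rates against a half-width that fits one rate, or from small subgroups whose own intervals are wider than ±0.12.

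What remains is not only a missing detail. The article attaches a precision figure to cut-offs, describes no data on which a derived cut-off could be checked independently, and names follow-up work for the factor structure but not for the cut-off.

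**Conclusion.** The point holds in a limited form. As described, a cut-off derived from this study's ROC would be assessed in the main sample that produced it, and ±0.12 does not cover the upward bias. Under a Youden-type rule with normal scores, AUC about 0.80, 28–30% positive and 100–200 participants, sensitivity is overstated by about 0.05–0.07, some 0.4–0.5 of its matching half-width. Specificity is overstated by about 0.02. Under a fixed-sensitivity rule the overstatement is about 0.02, for sensitivity only. The AUC is not affected by the choice of cut-off.

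The rule, the prevalence, the discrimination and the number with a reference diagnosis are all assumptions. Dropping items on the same data, which Internal consistency allows, would tend in the same direction but was not quantified. The correction is worth making because it is cheap, not because the bias would overturn the study.

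**What to change.** - State in advance how any ACB cut-off will be chosen.
- Repeat that choice inside a bootstrap (for example 500 resamples) and report optimism-corrected sensitivity and specificity next to the apparent values, with intervals.
- State that ±0.12 applies to a cut-off fixed beforehand, and give the number of participants it assumes.
- Label cut-offs provisional until tested in new participants. The second sample foreseen under Ethics and dissemination can serve only if reference measures are also collected there.

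The cost is a short script and slightly less favourable reported accuracy. The bootstrap is not a complete cure: in simulation it recovered about two thirds of the optimism, which is why the provisional label is still needed. Splitting the sample would remove the bias but costs more precision: with 150 participants and 28% positive, halving leaves 21 positives and widens the sensitivity interval from ±0.121 to 1.96 × √(0.16/21) = ±0.171. Collecting reference measures in the second sample would add burden there.
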